### Time Horizon

In the BNBD-NDD RCT, data collection occurred at baseline, 4 months, and 8 months. The reference case CEA and secondary CCA will use an 8-month time horizon, focusing on baseline and 8-month data; 8-month data are used to best capture the longer term costs and effects.

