### Sample Size Calculation

The BNBD-NDD RCT was powered to detect a group by time interaction across the 3 data collection time points (baseline, 4-month, and 8-month) and between the BNBD-NDD and usual care groups. The primary sleep outcome was the Disorders of Initiating and Maintaining Sleep (DIMS) [22] variable. To achieve a power of 0.80 with an α of .05, 39 participants per group would have to complete the DIMS measure at 8 months. Based on this analysis and the anticipated postenrollment dropout rate of 50% from a previous BNBD RCT, an estimated 160 participants were targeted for enrollment at baseline.

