### Outcomes for Economic Evaluation

PedsQL is an instrument that measures generic (rather than disease-specific) HRQoL and has been shown to have appropriate psychometric properties when used with children with NDDs [31]. It can be used to evaluate HRQoL in healthy children, youths, and those with medical conditions [32]. PedsQL uses a modular approach with 4 multidimensional scales on physical, emotional, social, and school functioning [33]. Parents rate each item using a 5-point Likert scale from 0 (never) to 4 (always) [31]. A Total Scale Score is calculated by adding all of the items and dividing the total by the number of items answered in all scales [33]. Mean Scale Scores are computed by dividing the sum of the items by the number of items answered in the scale [33]. Depending on the age of the participant's child, 3 parent-report versions were used (for ages 2-4 years, 5-7 years, and 8-12 years) to accommodate the age range of this study sample. The difference between the intervention and usual care groups’ average Total Scale Score in parent-proxy reports of their children’s PedsQL at baseline and 8 months will be evaluated in the reference case CEA. Secondary analyses will examine each of the 4 modules and age group trends; it is noted that inconsistent reporting of the school functioning section may occur due to age and the time of year of data collection (off-school period). The scoring and missing data (where applicable) will be completed in accordance with the PedsQL user manual [34].

In the CCA, the children’s sleep and parental outcomes are analyzed by comparing baseline and 8-month data and looking at changes in sample averages. Based on parent-reported questionnaire data, the DIMS score quantifies the severity of children's sleeping problems. The Single Item Fatigue Impact Scale [35] and the Depression, Anxiety, and Stress Scales [36] are used to evaluate the daytime fatigue and psychosocial health, respectively, of parents. Single Item Fatigue Impact Scale is adapted from the 40-item Fatigue Impact Scale [35]. The Depression, Anxiety, and Stress Scales have demonstrated adequate construct validity and high reliability [36].

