### Resource Use and Costing

#### BNBD-NDD Cost

The direct cost of BNBD-NDD to the families is primarily the retail cost of the intervention. As the program was offered free of charge for our RCT, we used the average of parents’ (proxy payers for their children) reported willingness to pay. The participating families were expected to have internet access, which was not assessed or included in the direct costs. Retail pricing will be explored further from the willingness to pay data, which obtained a hypothetical willingness to pay (HWTP) by directly asking for the maximum cost participants would pay for the program. The HWTP responses may contain hypothetical bias influenced by factors such as the absence of a budget constraint effect and strategic answering, as some may perceive their input to potentially affect future pricing [37].

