#### Treatment Utilization

The TU questionnaire [38] estimated the health care services families sought to address their children’s sleep problems, including publicly and privately funded ones. Care may be provided by family physicians, physician specialists (eg, pediatricians), and other health professionals (eg, psychologists). The mean frequency and costs of these services at baseline and at 8 months for the BNBD-NDD and usual care groups will be compared to see if BNBD-NDD impacted the usage rate. Out-of-pocket expenses reported for a health professional’s or provider’s help will also be assessed. Unit costs will be estimated using publicly available resources, such as the Canadian Agency for Drugs and Technologies in Health [39].

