#### Reference Case CEA

In the reference case analysis using the family payer perspective, the ratio of the difference in mean cost between groups to the difference in mean PedsQL total score per group will be used to estimate the ICER. An ICER will be calculated from the family’s perspective.

ICER = Costs_(BNBD-NDD + usual care)_ − Costs_(usual care)_ / Effect_(BNBD-NDD + usual care)_ − Effect_(usual care)_

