### Missing Data

Multiple imputation techniques are used to address missing data. This method works well for longitudinal data and is robust to violations of the nonnormality of the variables analyzed. Participants who do not complete both the baseline and the 8-month follow-up will not be included in the analysis. Where applicable, the measures’ user guides on missing data will be followed. For the PedsQL, the means of completed items in the scale will be imputed when 50% or more of the items are completed [34].

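### Completer-only use of baseline and 8-month data discards 4-month information and leaves the 8-month PedsQL contrast exposed to selective dropout

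*Protocol article*

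**What the plan says.** The Time Horizon section states that in the trial "data collection occurred at baseline, 4 months, and 8 months". It then sets the horizon of the reference-case cost-effectiveness analysis and the cost-consequence analysis at 8 months, "focusing on baseline and 8-month data; 8-month data are used to best capture the longer term costs and effects".

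The Outcomes for Economic Evaluation section applies this to the effect measure: the groups' "parent-proxy reports of their children’s PedsQL at baseline and 8 months will be evaluated in the reference case CEA". The Reference Case CEA section defines the ICER as "the ratio of the difference in mean cost between groups to the difference in mean PedsQL total score per group".

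The Missing Data section announces multiple imputation and then adds: "Participants who do not complete both the baseline and the 8-month follow-up will not be included in the analysis".

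The Sample Size Calculation section says that the trial itself was "powered to detect a group by time interaction across the 3 data collection time points", with DIMS as the primary sleep outcome. It requires 39 completers per group at 8 months, anticipates 50% dropout and targets 160 participants.

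**The concern.** Three stated choices act together: the effect is taken from two of three visits, only participants with both of those visits are analysed, and half the sample is expected to be lost. Multiple imputation is then left to fill gaps only among people who completed both visits. It does nothing for those who left between months 4 and 8, the group for whom an intermediate measurement is most informative.

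At stake is the denominator of the reference-case ICER. Suppose families who saw little early change leave more often in one arm than in the other. The completers' 8-month difference then no longer estimates the difference in the randomised population. The 4-month data are the part of the trial record that could reveal and partly correct this.

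**Working it through.** **1. The plan's own figures.** 39 per group × 2 = 78 completers. 78 / (1 − 0.5) = 156, consistent with the stated target of 160. From 160, half retained and split 1:1 gives 160 × 0.5 / 2 = 40 completers per arm out of 80 randomised. The 39 cannot be re-derived, because the article gives no effect size, SD or correlation.

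**2. Exposure to selective dropout.** Let b be the slope of the 8-month score on the 4-month score, given baseline. If dropout depends on the 4-month score, the completers' 8-month mean in an arm is shifted by b × (completers' mean minus everyone's mean at month 4, baseline-adjusted). The contrast is biased by b × (shift in intervention arm − shift in usual-care arm). With equal variances at the two visits, b equals the baseline-adjusted correlation r. For the assumed r of 0.33 to 0.7 used below, each PedsQL point of differential shift at month 4 moves the 8-month contrast by 0.33 to 0.7 points. If the shift is equal in both arms, the contrast is not biased. The article gives no figure for the shift.

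**3. Precision.** Let n8 be the number per arm with 8-month data and n4 the number with 4-month data (monotone dropout, large-sample approximation). The variance of the 8-month contrast, relative to completers only, is (1 − r²) + r² × n8/n4. Take n8 = 40; n4 and r are assumptions.

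- n4 = 40 (nobody seen at month 4 only): ratio 1, no gain for any r.
- Compound symmetry, correlation ρ between any two visits: r = ρ/(1 + ρ). For ρ = 0.5, r = 0.33; with n4 = 50 the ratio is 1 − 0.111 × 0.2 = 0.978 (2% reduction). For ρ = 0.8, r = 0.44; with n4 = 80 the ratio is 1 − 0.198 × 0.5 = 0.901 (10%).
- Correlation decaying with time, 0.6 to 0.8 between adjacent visits: r = 0.51 to 0.62. With n4 = 50 and r = 0.51 the ratio is 1 − 0.265 × 0.2 = 0.947 (5%). With n4 = 60 and r = 0.62 it is 1 − 0.390 × 0.333 = 0.870 (13%).
- r = 0.7 and n4 = 60: 1 − 0.49 × 0.333 = 0.84 (16%).

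The range is 2-16% of variance. As √0.978 = 0.99 and √0.84 = 0.92, intervals would be about 1-8% narrower.

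**4. What an area-under-the-curve effect would measure.** With no baseline difference and effects e4 and e8, the trapezoid mean over 0-8 months is (2 × e4 + e8)/4. For e8 = 1 this is 0.25 if nothing is gained by month 4 (e4 = 0), 0.50 if the gain is linear (e4 = 0.5), 0.75 if it is complete by month 4 (e4 = 1), and 1.25 if it halves after month 4 (e4 = 2). Relative to the 8-month contrast, and under compound symmetry with ρ of 0.5 to 0.8, the z-value is multiplied by about 0.4 (late), 0.8 (linear) or 1.15-1.2 (complete by month 4). An area under the curve is therefore a different quantity and is not reliably more precise.

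**The case against.** The strongest defence is that the end-of-follow-up effect is deliberate, reasoned and coherent. The ICER is a cost per PedsQL point, not per unit of utility-weighted time, so nothing obliges the plan to integrate over the horizon. This stands.

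A reader might infer that costs accumulated over 8 months are being divided by a reading at one moment. The article does not support that. "The direct cost of BNBD-NDD to the families is primarily the retail cost of the intervention", a single price proxied by stated willingness to pay. For services it compares "The mean frequency and costs of these services at baseline and at 8 months", and the limitations speak of 12-month service use. No passage describes costs summed over months 0 to 8. That 12-month recall sits awkwardly with an 8-month horizon, but this is a separate matter.

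A reader might also infer that the ICER is wrong because it ignores how early the benefit arises. It is not: the factors in step 4 convert it into a different quantity and do not measure an error in it. Nor does leaving out month 4 lose precision in general, since the loss among completers is zero.

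Two further objections have force. The article does not say that PedsQL or service use was collected at month 4; only DIMS is tied to the three-visit design. And the harm comes from the exclusion rule more than from the choice of horizon. Both shape the fix, but neither removes the point.

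Finally, modelling detail may properly sit in an analysis plan that is not shown. The exclusion of non-completers, however, is stated outright in the article.

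**Conclusion.** The point holds in a limited form. As written, the plan excludes participants seen at 4 but not at 8 months, and the 8-month contrast rests on the roughly half of the sample expected to complete. The main consequence is exposure to dropout that is related to early response and differs by arm. The documents allow its mechanism to be shown but not its size. The gain in precision is secondary. The 2-16% depends on assumed correlations and an assumed 50 to 80 per arm still seen at month 4, with the top figure taken at 60 per arm. The 8-month horizon, the end-point ICER and the enrolment target are not in error. This is a worthwhile, inexpensive improvement to a stated rule, and it can still be made because the article reports the economic data as cleaned but not yet analysed.

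**What to change.** Keep the 8-month between-group PedsQL difference as the reference-case effect. In the Missing Data section, remove the exclusion of participants without both visits, and state that the contrast is estimated from all randomised participants with any follow-up, adjusted for baseline PedsQL and diagnosis stratum.

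- If PedsQL was taken at 4 months: fit a repeated-measures model to baseline, 4-month and 8-month scores and read off the 8-month contrast.
- If it was not: impute 8-month PedsQL by multiple imputation, with 4-month DIMS and any 4-month parent measures as auxiliary variables.

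State which of the two applies, and compute costs and effects on the same participants. Report the completer analysis alongside as a sensitivity check. An area-under-the-curve ICER may be added as an optional secondary result if 4-month PedsQL exists.

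The cost is slightly more analysis of data already collected, and reliance on a missing-at-random assumption that should be stated openly. The reference-case quantity does not change.

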### Outcomes for Economic Evaluation

PedsQL is an instrument that measures generic (rather than disease-specific) HRQoL and has been shown to have appropriate psychometric properties when used with children with NDDs [31]. It can be used to evaluate HRQoL in healthy children, youths, and those with medical conditions [32]. PedsQL uses a modular approach with 4 multidimensional scales on physical, emotional, social, and school functioning [33]. Parents rate each item using a 5-point Likert scale from 0 (never) to 4 (always) [31]. A Total Scale Score is calculated by adding all of the items and dividing the total by the number of items answered in all scales [33]. Mean Scale Scores are computed by dividing the sum of the items by the number of items answered in the scale [33]. Depending on the age of the participant's child, 3 parent-report versions were used (for ages 2-4 years, 5-7 years, and 8-12 years) to accommodate the age range of this study sample. The difference between the intervention and usual care groups’ average Total Scale Score in parent-proxy reports of their children’s PedsQL at baseline and 8 months will be evaluated in the reference case CEA. Secondary analyses will examine each of the 4 modules and age group trends; it is noted that inconsistent reporting of the school functioning section may occur due to age and the time of year of data collection (off-school period). The scoring and missing data (where applicable) will be completed in accordance with the PedsQL user manual [34].

In the CCA, the children’s sleep and parental outcomes are analyzed by comparing baseline and 8-month data and looking at changes in sample averages. Based on parent-reported questionnaire data, the DIMS score quantifies the severity of children's sleeping problems. The Single Item Fatigue Impact Scale [35] and the Depression, Anxiety, and Stress Scales [36] are used to evaluate the daytime fatigue and psychosocial health, respectively, of parents. Single Item Fatigue Impact Scale is adapted from the 40-item Fatigue Impact Scale [35]. The Depression, Anxiety, and Stress Scales have demonstrated adequate construct validity and high reliability [36].

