**Objective:**

This protocol outlines an economic evaluation conducted alongside the BNBD-NDD randomized controlled trial (RCT) that aims to assess its costs, efficacy, and cost-effectiveness compared to usual care.

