### Data Analysis

#### Overview

For the reference case CEA analysis, the mean sample PedsQL at baseline and 8 months will be compared. Regression analyses will examine the impacts of baseline characteristics (geographical region, age groups, sex, household income, and NDD diagnosis) on the efficacy measures. For all regression analyses, the mean difference between groups will be reported, as well as the variance, *P* value, and goodness of fit using *R*^2^.

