#### Secondary CCA

The CCA will assess the impacts on children’s sleep disturbance severity, parents’ daytime functioning, and psychosocial health. It adopts a broader perspective, providing a wider range of relevant costs and outcomes [24]. This allows various decision makers to focus on aspects and contexts specific to them [24]. The costs examined will extend beyond the family and include the costs of reported publicly and privately funded services sought.

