## Discussion

In this paper, we have described an economic evaluation protocol for the BNBD-NDD eHealth intervention, which aims to improve insomnia in children with NDDs. The economic evaluation will identify, measure, and value the costs and outcomes of BNBD-NDD compared to usual care. The reference case CEA will assess the costs and QoL of the children, and the CCA will examine measures beyond QoL for the children and their caregivers.

The prevalence of sleep disorders has been observed to be higher in children with NDDs relative to TD children [40]. BNBD-NDD has the potential to deliver an evidence-based and cost-effective insomnia intervention to children with NDDs, which is critically important given the lack of available treatments. The eHealth delivery system may also overcome some existing barriers to treatment access. If cost-effective, this program can improve sleep outcomes and positively affect the well-being of children with NDDs and their caregivers. To our knowledge, BNBD-NDD is the first eHealth insomnia intervention for children with NDD. No published reports have evaluated internet-based interventions for insomnia in preschool- and school-aged children; 1 study has reported an effective internet intervention for sleep disturbances in infants and toddlers [41].

Some limitations of this study are the uncertainties with cost estimates, the parental-reported measures on behalf of the children, the recall bias of their children’s 12-month service usage, and the lack of objective outcome data. With family and societal payer perspectives, the breadth of the costing analysis is limited by the collected cost data in the RCT and thus likely to be an underestimation of real-world costs. While the CCA provides a wider scope of relevant outcomes and costs for decision makers, the interpretation of the results may be prone to subjective bias [24]. The BNBD intervention would benefit from real-world evidence to evaluate its effectiveness and also explore its applicability to children with other medical conditions.

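### The cost-consequence analysis states no between-arm contrast for child sleep (DIMS), parental fatigue and parental psychosocial health; as worded it permits a pre-post reading

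*Protocol article*

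**What the plan says.** In the protocol article, Outcomes for Economic Evaluation, the CCA's child sleep and parental outcomes "are analyzed by comparing baseline and 8-month data and looking at changes in sample averages". The outcomes meant are DIMS, the single-item fatigue scale and the Depression, Anxiety, and Stress Scales (DASS). This is the only sentence that says how they are analysed. The Secondary CCA section states the purpose, "The CCA will assess the impacts on children’s sleep disturbance severity, parents’ daytime functioning, and psychosocial health", and gives no contrast.

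Two neighbouring comparisons do name the arms. For PedsQL, the same section refers to "The difference between the intervention and usual care groups’ average Total Scale Score in parent-proxy reports of their children’s PedsQL at baseline and 8 months". For treatment utilization, mean frequencies and costs "at baseline and at 8 months for the BNBD-NDD and usual care groups will be compared to see if BNBD-NDD impacted the usage rate".

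The Overview under Data Analysis again uses looser wording for PedsQL: "the mean sample PedsQL at baseline and 8 months will be compared". The Reference Case CEA section, however, builds the ICER from differences between arms.

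**The concern.** A change in a sample average from baseline to 8 months contains everything that happened in those months, not only the programme. Children entered because they currently met insomnia symptom criteria (Inclusion Criteria), so some improvement in mean DIMS can be expected without treatment. The two assessments also fall at different times of the year, and the article itself notes that the school calendar affects part of the PedsQL. Randomisation deals with these influences only if the arms are contrasted, and for these three outcomes no contrast is written down.

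The article intends the results to inform families and possibly public funders. A reader of the CCA table could take an improvement over time for an effect of the programme.

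**Working it through.** **1. What each section fixes**

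| Outcome | Where | Contrast stated |
|---|---|---|
| PedsQL total | Outcomes for Economic Evaluation; Reference Case CEA | Between arms |
| PedsQL total | Data Analysis, Overview | Baseline and 8 months; arms not named |
| Treatment utilization | Treatment Utilization | Between arms |
| DIMS, fatigue, DASS | Outcomes for Economic Evaluation | Baseline to 8 months; arms not named |
| DIMS, fatigue, DASS | Secondary CCA | None |

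PedsQL has loose wording in one place and a between-arm definition in two others. The three CCA outcomes have only the loose wording.

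**2. What each reading estimates**

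Let *s* be the mean change that would occur without the programme (time trend plus any regression to the mean) and *d* the added change due to the programme. With 1:1 allocation:

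- change in the whole sample, arms pooled: *s* + *d*/2
- change in the intervention arm: *s* + *d*
- change in the usual care arm: *s*
- difference between arms: (*s* + *d*) − *s* = *d*

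Only the last isolates the programme. The quoted sentence is compatible with any of the first three, and also with calculating the changes per arm and then comparing them.

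**3. Can *s* be sized?**

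Not from the document. It gives no DIMS mean, SD, entry displacement or test-retest correlation. Entry was on symptom criteria lasting at least a month, not on a DIMS cut-off, and parents were not selected on fatigue or DASS.

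**4. Precision, if changes are compared between arms**

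The plan's own figures come first. Sample Size Calculation gives 39 completers per group and 50% dropout: 39 / (1 − 0.5) = 78 per arm, 156 in total, which is consistent with the rounded target of 160. This target does not depend on the present point; I use only n = 39 per arm.

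Let *r* be the correlation between baseline and 8 months, with equal SDs at both times. In SD units:

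- difference in raw change: SE = √[(2/39) × 2(1 − *r*)]
- baseline-adjusted difference: SE = √[(2/39) × (1 − *r*²)]
- ratio of variances, adjusted to raw: (1 + *r*)/2

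The correlation is an assumption, shown at two values:

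| *r* | SE, raw change | SE, adjusted | 95% half-width, raw | 95% half-width, adjusted | Narrower by |
|---|---|---|---|---|---|
| 0.5 | √(0.0513 × 1.00) = 0.226 | √(0.0513 × 0.75) = 0.196 | 0.44 | 0.38 | 1 − √0.75 = 13% |
| 0.7 | √(0.0513 × 0.60) = 0.175 | √(0.0513 × 0.51) = 0.162 | 0.34 | 0.32 | 1 − √0.85 = 8% |

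For any *r* below 1 the ratio (1 + *r*)/2 is below 1, so the adjusted contrast is the more precise of the two.

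**The case against.** The strongest reply is that the sentence is shorthand. The objective "aims to assess its costs, efficacy, and cost-effectiveness compared to usual care", and the Discussion says: "The economic evaluation will identify, measure, and value the costs and outcomes of BNBD-NDD compared to usual care". The trial was powered on a group-by-time interaction with DIMS as its primary sleep outcome. The Overview says that regressions will report mean differences between groups. Most tellingly, the Overview uses similar loose wording for PedsQL, whose comparison is plainly between arms elsewhere. Much of this stands, and it makes a between-arm intention likely.

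Two stronger inferences therefore fail. A reader might infer that the CCA is designed as an uncontrolled analysis in which the usual care arm plays no part. No sentence says that the arms are pooled or that within-arm change is taken as the effect, and the utilization costs, which belong to the CCA, are compared between arms. A reader might also put a number on regression to the mean from an assumed displacement and correlation. That calculation suits selection on the DIMS score itself, which is not how children entered, and it does not carry over to parents.

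The reply does not close the gap. The objective and Discussion state an aim, not an analysis. The interaction is the basis for the trial's power and is not given as the CCA analysis. The covariates listed for the regressions do not include treatment arm, so it is unclear which groups are meant.

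It can also be said that an article leaves the estimator to a fuller plan. If the article were merely silent, there would be no finding. Here it states an analysis, and that analysis omits the contrast. A difference in change would also be a valid controlled contrast; baseline adjustment is preferred for precision.

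**Conclusion.** The point holds as an ambiguous and badly fixed contrast. For DIMS, fatigue and DASS, the only stated analysis is a change in sample averages over time, with no arms named. Followed literally, it would not deliver the impacts that the Secondary CCA section promises: it mixes them with time trends and, for DIMS, with regression to the mean. How large that mixture would be is unknown on these documents.

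On the more likely reading, that changes are compared between arms, there is no such bias from a shift common to both arms, but precision is lost. The loss is modest: intervals about 13% or 8% wider than they could be, taking the adjusted interval as the narrower by those amounts, at assumed correlations of 0.5 and 0.7. This rests on 39 completers per arm and equal SDs at both times. The reference case ICER is not affected beyond the need to align one sentence.

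**What to change.** - In Outcomes for Economic Evaluation and Secondary CCA, state that DIMS, parental fatigue and DASS are each reported as the between-arm difference at 8 months, adjusted for the outcome's baseline value and the NDD diagnosis stratum used in randomisation, with a 95% CI. State that within-arm changes are descriptive only.
- In the Data Analysis overview, reword the PedsQL sentence so that it matches the between-arm definition in Outcomes for Economic Evaluation and Reference Case CEA.

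The cost is a few sentences and a standard model on data already collected. The Results section says that the economic data are cleaned and being prepared for analysis, so the clarification can still come before the results.
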